## Abstract

•Hip fractures are associated with increased morbidity, mortality, and substantial economic costs.•A randomized controlled trial is design to compare home-based physical intervention and standard care.•The primary outcome is the assessment of occurrence of secondary falls in elderly hip fracture patients.

Hip fractures are associated with increased morbidity, mortality, and substantial economic costs.

A randomized controlled trial is design to compare home-based physical intervention and standard care.

The primary outcome is the assessment of occurrence of secondary falls in elderly hip fracture patients.

## Introduction

1

Falls and fractures in older people are of major public health significance. One in three older people experience one or more falls each year [1] and about one in six 50-year-old women will have at least one hip fracture before they die [2]. This propensity for fall-related injury in elderly persons stems from a high prevalence of comorbid diseases such as osteoporosis and age-related physiological decline (e.g. slower reflexes) that make even a relatively mild fall, potentially dangerous. With a rising elderly population, hip fracture incidence and cost are expected to grow substantially [3]. It is estimated that by 2050 the total global cost of hip fractures will be $131.5 billion annually [4]. Unfortunately, outcomes after hip fracture are often poor [5] with high mortality rates and decreased functionality and mobility in survivors [6]. Henceforth, fall is major giant of elderly people in community settings [7]. It poses major social, psychological and economic burden to individuals and their families.

In Pakistan, there is a lack of large scale epidemiological studies resulting in lack of statistical data on hip fractures. An ultrasound based study conducted throughout the country concluded that currently there are 9.91 million people suffering from osteoporosis [8]. They further added that the numbers estimated will rise up to 11.3 million by 2020 and 12.91 million by 2050. In addition, 75% of the patients suffering from osteoporosis in Pakistan have had hip fractures [9]. On the other hand, considering low capital per income, the overall cost for treating patients with hip fracture is very high eventually leading to increased healthcare burden.

Total hip replacement (THR) remains the ultimate treatment option for patients suffering from hip fractures and severe hip osteoarthritis [10]. Rehabilitation after hip fracture surgery is the most critical component of post-surgical care and has been associated with better functional outcomes [10]. According to McMeeken & Galea (2007), the key feature of THR rehabilitation program is strengthening of muscles around the affected joint and improvement in gait and joint stability. A systematic review of 88 trials conducted in 2016 reports significant effect of home-based exercise program post-surgery on strengthening of leg muscles and overall functionality [11]. However, adherence to exercise programs is a major issue identified in both public health researches and clinical practice. There is an evidence that long term adherence to exercise may be better with home-based rehabilitation programs rather than institution-based programs especially for older adults [12].

The development and implementation of effective rehabilitation strategies to minimize disability and secondary falls predominantly among older people is an urgent public health challenge due to the increasing proportion of older people in the global world [13], [14], [15]. Around 962 million people worldwide are aged 60 years and older [16] and this number is predicted to increase to 2.1 billion by 2050 which will represent one eighth of the global population [17]. Developing countries are predicted to have a 140 percent increase in older people by 2030 [18]. A study conducted by students and faculties at nurse-managed clinic in US concluded that recurrent falls are a common reason for admission of previously independent elderly persons to long-term care institutions [19]. Bezon et al. [20] conducted a study in British community reported falls to be a major reason for 40% of nursing home admissions. Fear of falling and the post-fall anxiety syndrome are also well recognized as negative consequences of falls. The loss of self-confidence to ambulate safely can result in self-imposed functional limitations [21], [22], [23].

For many individuals, the risk of falls and disability after hospital discharge decreases with time. However, for a significant proportion, this is not the case [24]. Many patients after discharge are readmitted with second fracture to the hospitals due to lack of acute rehabilitation programs [25]. Therefore, we have designed a post-discharge home-based physical rehabilitation intervention program to minimize disability and falls in this high-risk elderly population. This study will evaluate the effectiveness of 12 week home-based physiotherapy program in reduction of secondary falls and improvement in physical mobility of elderly patients after hip fracture surgery.

## Methods

2

### Study design

2.1

This study will be an open label, simple randomized controlled trial at a single hospital. The two arms will be equally allocated on a 1:1 ratio into intervention and control groups. The control arm will receive the usual standard postoperative rehabilitation after a bipolar hemiarthroplasty/total hip arthroplasty which will include in hospital rehabilitation and a maximum of 5 physiotherapist visits postoperatively, arranged and funded by the patient as feasible. The intervention group will receive an extended home-based rehabilitation program twice a week continued for 3 months (12 weeks) after discharge funded by the study.

### Recruitment

2.2

The study will be conducted solely at Aga Khan University Hospital. The care providers involved with the study will include Orthopaedic consultants, Family medicine physician, physiotherapist, and Orthopaedic nurses. We will recruit 224 elderly patients aged 60 years and above undergoing hip fracture surgery who will be randomly divided into intervention and control arms. Participants will be enrolled by research-assistant over a 19‐month period from Emergency Room and Orthopedic outpatient clinics. This study will be conducted over a period of 24 months with ongoing recruitment and follow-ups after intervention.

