#### Primary outcome

2.5.1

The Primary outcome of the study is occurrence of falls. Falls will be measured at 3, 6, 12, and 24 months by research-assistant follow-up telephone calls for both the groups. A structured pre-tested questionnaire will be used to assess falls on telephonic interview. The interview will take 5–10 minutes of each participants to assess occurrence of any new fall incident after discharge. Falls will be assessed by comparing the number of falls in intervention and control groups.

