### Follow-ups

2.6

For follow-ups, telephone calls and face to face interviews will be utilized. All the Patients (both groups) will be contacted after 3 months, 6 months, 12 months, and 24 months (Fig. 1) for the period of two years via telephone call to assess occurrence of fall. The call will take approximately 5–10 minutes of each patient. While, the performance-based mobility measure will be marked at every routine follow-up for up to two years using face to face interview to assess the overall trend. Furthermore, anthropometric assessment will also be done to assess weight loss at each follow-up.

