### Statistical analysis

2.10

Intention to treat Analysis will be performed for both the groups. All the analysis will be done on STATA version 15.0 [32]. Baseline characteristics for both groups and changes from baseline to 6 months and baseline to 2 year will be compared in the two groups using the χ2 test, Mann-Whitney, or Student's t-test as applicable. The number of falls in both the groups will be compared by computing incidence ratio rates using negative binomial regression models after adjusting for baseline differences in fall rates along with incomplete/loss to follow‐up in a small percentage of subjects. Between group comparisons of final test performance for the continuously-scored outcome measures will be made using General Linear Models (ANCOVA) controlled for pre-test performance.

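### The stated study period (24 months, 19 of them enrolling) contradicts the 24-month falls call and the 2-year comparison; at least 43 months would be needed

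*Protocol article*

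**What the plan says.** Section 2.2 (Recruitment) gives both durations in adjacent sentences. On enrolment: "Participants will be enrolled by research-assistant over a 19‐month period". On the whole study: "This study will be conducted over a period of 24 months with ongoing recruitment", and the same sentence goes on to include follow-up after the intervention in that period. The recruitment target is 224.

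The other sections set a two-year horizon per patient:

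- Section 2.5.1 (Primary outcome): "Falls will be measured at 3, 6, 12, and 24 months". Falls are counted from discharge.
- Section 2.6 (Follow-ups) applies the same four calls to all patients in both groups, "for the period of two years via telephone call to assess occurrence of fall". Mobility is measured face to face at routine visits, with two years as an upper limit.
- Section 2.10 (Statistical analysis): "changes from baseline to 6 months and baseline to 2 year will be compared in the two groups". It also plans negative binomial models for falls and expects incomplete follow-up in only a small fraction of subjects.

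No text in the article extends the study beyond 24 months or names a common cut-off date.

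**The concern.** Read as written, section 2.2 fits enrolment and follow-up together into 24 months, while section 2.6 gives each patient a call 24 months on. A patient who joins in month 19 would have 5 months before the study closes.

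Two things are at stake if section 2.2 is the operative statement. The last scheduled falls assessment and one of the two change intervals named in section 2.10 could not be delivered. The 12-month call would also be missed by a sizeable group for calendar reasons alone, before any death, withdrawal or lost contact. If the conflict is left open, the time horizon of the primary outcome might be settled only after data have accumulated, which is undesirable in an open-label trial.

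**Working it through.** **Inputs.** Enrolment period A = 19 months, study period T = 24 months and N = 224 (all section 2.2). Calls at f = 3, 6, 12 and 24 months (sections 2.5.1 and 2.6). The article states no share of patients expected to reach each call, so there is no figure of its own to reproduce on this point.

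**Step 1: no accrual assumption.** A patient enrolled at month t has at most T − t months of follow-up.

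- Last enrolled: 24 − 19 = 5 months.
- First enrolled: 24 − 0 = 24 months.
- Reaching month 24 requires t = 0. If the clock starts at discharge, even a day-one patient falls short.
- Duration needed for every patient to reach month 24: 19 + 24 = 43 months.

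**Step 2: uniform accrual (my assumption; the article gives no accrual pattern).** Share able to reach call f = min(19, 24 − f)/19, clock from enrolment.

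| Call | Share | Patients of 224 |
|---|---|---|
| 3 months | 19/19 = 100% | 224 |
| 6 months | 18/19 = 94.7% | about 212 |
| 12 months | 12/19 = 63.2% | about 141 |
| 24 months | 0/19 = about 0% | about 0 |

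The share unable to reach month 12 is 7/19 = 36.8%.

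**Step 3: sensitivity at month 12.** Let the cumulative accrual be (t/19)^k, so the share unable to reach month 12 is 1 − (12/19)^k.

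- k = 0.7 (front-loaded): 27.5%
- k = 1 (uniform): 36.8%
- k = 1.25: 43.7%
- k = 2 (slow start): 60.1%
- Uniform, with the clock starting half a month after enrolment: 1 − 11.5/19 = 39.5%

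The same formula with 18 in place of 12 gives 3.7% (k = 0.7) to 10.2% (k = 2) unable to reach month 6. Month 24 is about 0% attained in every case.

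**Step 4: person-time under uniform accrual.** Mean possible follow-up = 24 − 19/2 = 14.5 months. Total = 224 × 14.5 = 3,248 person-months, against 224 × 24 = 5,376 planned, and 3,248/5,376 = 60%. With a constant fall rate and pure Poisson counts, the standard error of the log rate ratio would rise by a factor of √(5,376/3,248) = 1.29. Overdispersion, which the negative binomial model allows for, would make the increase smaller.

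**The case against.** The strongest reply is that the 24-month study length appears once, in a loosely worded sentence, whereas two years of patient follow-up recurs in several sections. Section 2.2 may simply be a drafting slip, with 24 months meant as follow-up per patient or as a funding period. Fig. 1, which sections 2.4 and 2.6 cite, could not be seen in the text at hand. This stands as a reason to make every loss figure conditional on section 2.2. It does not remove the contradiction: that sentence describes the whole study and includes recruitment, so on the charitable reading it is the sentence that needs correcting.

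Four stronger readings are tempting, and the documents do not support them.

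- **That the primary outcome cannot be delivered.** Section 2.5.1 does not make month 24 the primary time point, months 3 and 6 are largely attainable, and the negative binomial model can use unequal follow-up given an exposure term. What cannot be rescued is the 24-month assessment and the 2-year change.
- **That 37% will miss month 12.** This needs uniform accrual, which is nowhere stated.
- **That every section requires 24 months from every patient.** Only section 2.6 says so, and only for the telephone calls. Mobility has two years as a ceiling, and section 2.10 names a comparison.
- **That the 20% attrition allowance in section 2.7 is breached.** That allowance is tied to no visit, and the 40% and 20% fall proportions to no time horizon, so the comparison is not like for like. The fairer yardstick is the small fraction of incomplete follow-up expected in section 2.10, which would be clearly exceeded at month 12.

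**Conclusion.** The point holds as an internal contradiction that must be reconciled. Section 2.2 cannot stand together with sections 2.5.1, 2.6 and 2.10 as written, and showing this needs only the article's own figures.

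The consequences depend on which statement governs. If section 2.2 does, month 24 is out of reach for essentially everyone, whatever the accrual pattern. The share missing month 12 is about 37% under uniform accrual, roughly 27% to 60% across the accrual shapes tried, and 39.5% under uniform accrual with a half-month delay in the clock. Person-time would be about 60% of that planned, again under uniform accrual. If the two-year follow-up governs, no data are lost, and the error lies in the stated study duration.

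**What to change.** **Preferred.** Amend section 2.2 to give a study duration of at least 43 months (19 of enrolment plus 24 of follow-up). After month 19 only the remaining telephone calls and face-to-face mobility and anthropometric visits for enrolled patients would continue. The cost is a protocol amendment and a longer period of staffing for calls and visits.

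**If the study must close at month 24.** Say so, and then:

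1. Remove the 24-month falls time point from sections 2.5.1 and 2.6 and the baseline-to-2-year comparison from section 2.10.
2. Set one common close-out date and add one close-out call per patient. The scheduled calls alone would leave falls after the last completed call uncounted.
3. Analyse falls from discharge to close-out or last contact by negative binomial regression with log(observed time) as offset. Possible follow-up is 5 to 24 months from enrolment, and slightly less from discharge.
4. State the reduced person-time and the resulting precision. The present sample size was not derived for this analysis, so its adequacy should be shown and not assumed.

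The cost of this route is giving up the two-year claim, plus the close-out call. Whichever route is taken, it should be fixed before outcome data accumulate.

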#### Inclusion criteria

2.2.1

To be included in the study patients must meet the following inclusion criteria: 1) age ≥ 60 years; 2) able to walk independently with or without a walking frame prior to the fracture; 3) diagnosis of proximal femoral fracture; 4) history of fall; 5) surgical procedure Bipolar hemiarthroplasty / total hip replacement and postoperative ambulatory status weight bearing as tolerated.

#### Exclusion criteria

2.2.2

Patients will be ineligible to participate in the study if they are unable to walk more than one meter despite assistance with a walking aid and/or another person, are legally blind, have a progressive neurological disease (e.g. Parkinson’s disease, dementia) or low Conscious level (low GCS) or suffer from any medical condition precluding exercise (e.g. unstable cardiac disease) or other uncontrolled chronic conditions that would interfere with the safety and conduct of the training and testing protocol or interpretation of results. Moreover, Patients undergoing dynamic hip screw (DHS) will be excluded from the study due the different postoperative weight bearing regimens including non-weight bearing, toe touch, partial and full weight-bearing. Most of the patients with a bipolar hemiarthroplasty/ total hip arthroplasty are allowed full weight bearing postoperative and this will therefore keep the groups homogenous. We will utilize medical record files to assess eligibility criteria of patients for participation in the study.

### Home-based rehabilitation program

2.3

Home-base rehabilitation program is an extended 12 weeks home-based strength retraining program of progressive balance and lower limb strengthening exercises twice a week for 3 months as well as evidence based cueing strategies to reduce freezing of gait. All exercises will include 5 minutes warm-up exercises. The lower limb extensor muscle groups, which act to prevent collapse of the lower limb (hip & knee extensors and ankle plantar flexors) will be targeted with exercises designed to enhance postural control (i.e. balance) and muscle strength. The balance exercises include standing with a decreased base of support, forwards and sideways stepping/walking, and graded reaching activities in standing. Strengthening exercises will include sit-to-stand, forward and lateral step-ups onto a small block, semi squats and heel raises in standing. Standard principles governing frequency, volume, duration, intensity and progression of exercise will be applied. Cueing strategies will be used to reduce freezing. These will include identifying appropriate methods of cueing (cognitive, auditory, and somatosensory) for each participant and incorporating these cues into everyday activities.

The physiotherapists will deliver home-based rehabilitation program with sufficient clinical experience with older population. For each patient randomized to the intervention group, a physiotherapist will visit the patient’s home and will prescribe a selection of exercises at the first visit. The same physiotherapist will return twice a week for 3 months to make progressive adjustments to the exercise protocol according to the home-base rehabilitation program exercise manual.

### Data collection

2.4

Participant will be enrolled into the study after the informed consent process has been completed, and the patients have met eligibility criteria. Patient consent for study participation will be obtained during the hospital stay by the research-assistant. Also, medical clearance will be required from each patient’s primary surgeon to certify him / her as able to participate in moderate-intensity rehabilitation program before taking part in the study. A research-assistant will perform a baseline assessment using a pre-structured questionnaire to assess baseline characteristics including age, gender, marital status, educational status, socio-economic, BMI, past medical history, medication, assessment of neurological status (Glasgow coma scale (GCS) will be used to assess conscious level of patient) functional status, use of ambulatory aids, number of previous falls, Type of fracture, and surgical repair type. A physiotherapist will perform assessment of mobility-related disabilities using performance-based mobility measure at baseline. The scores at baseline will be recorded for all the patients (intervention and control arms). Lastly, fall risk assessment, geriatric assessment, and general fall prevention teaching will be done by geriatric expert physician at the time of enrolment for both the groups. All the measurements will be done before hip fracture surgery (preoperative assessment). All the adverse events (defined as a significant injury or medical event that causes the participant to seek attention from a health professional or limit their activities) will be monitored and recorded throughout the study during the follow-up telephone calls to each participant. All the adverse events will be covered through institutional insurance coverage. Fig. 1 shows the details of participant’s recruitment, randomization, and follow-up.

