#### Secondary outcome

2.5.2

Physical Mobility and Mobility-related disability will be measured with a self-reported test at every routine follow-up for up to two years using a performance-based test as per Haley et al. [26]. The performance-based mobility measure will be the lower extremity Summary Performance Score version of the Short Physical Performance Battery (SPPB) [27]. This battery gives a composite score based on timed performance of three mobility tasks: the ability to stand up for up to 10 seconds with feet in different positions (together side by side, semi-tandem and tandem), 4-meter walk and time to rise from a chair 5 times. The short performance based mobility tool is a valid and reliable tool with test retest validity ranging from 0.83 to 0.89. Study conducted by Gómez and colleagues in 2013 on adults between 65 to 74 years of age residing in the Andes Mountains of Colombia reported Test-retest reliability of 0.87 of the SPPB in Spanish version [28]. Another study conducted in Quebec and Brazil by Freire and colleagues in 2012 reported the validity and reliability of SPPB in diverse populations ranging from 0.83 to 0.89 [29]. This short performance battery tool had been validated in varied languages in different regions but not in Urdu language. Therefore, to use this tool in the study, we will perform back and forward translation of SPPB in Urdu language and will send it to 5–7 clinical experts to rate it for clearance and relevance in order to calculate the validity of tool in Urdu language.

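### The only mobility baseline is taken before hip fracture surgery, so adjusting the follow-up SPPB for it will probably gain little or no precision

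*Protocol article*

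**What the plan says.** Section 2.4 (Data collection) includes mobility in the baseline assessment: "A physiotherapist will perform assessment of mobility-related disabilities using performance-based mobility measure at baseline". It covers both arms: "The scores at baseline will be recorded for all the patients (intervention and control arms". The same section then fixes the timing: "All the measurements will be done before hip fracture surgery (preoperative assessment".

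Section 2.5.2 (Secondary outcome) names the measure as the "lower extremity Summary Performance Score version of the Short Physical Performance Battery (SPPB"). Its tasks are timed standing in three foot positions, a "4-meter walk and time to rise from a chair 5 times".

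Section 2.10 (Statistical analysis) uses the baseline. Final scores on continuous outcomes are compared by "General Linear Models (ANCOVA) controlled for pre-test performance", and changes from baseline to 6 months and to 2 years are also compared between groups.

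Two eligibility rules bear on the timing. Section 2.2.1 requires "postoperative ambulatory status weight bearing as tolerated". Section 2.2.2 excludes patients who are "unable to walk more than one meter despite assistance with a walking aid" or another person's help. No section describes an SPPB taken after surgery or at discharge, or a recalled pre-fracture score.

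**The concern.** The SPPB requires standing, walking and rising from a chair. A patient waiting for hemiarthroplasty or hip replacement for a proximal femoral fracture will probably be unable to do most of it. Two things follow if most baseline scores sit at the minimum.

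- The ANCOVA covariate hardly varies, so it explains little of the spread in final scores, and the adjustment does little of what it was chosen for.
- Change from baseline is close to the final score itself. It mainly records recovery from the fracture and operation, which both arms share. It says little about the effect of a home programme that starts only after discharge (Section 2.1).

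A preoperative baseline also sits badly with an eligibility rule about postoperative weight bearing. The order of enrolment, baseline, surgery and allocation therefore needs to be clear.

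**Working it through.** **Stated figure.** The protocol gives no SPPB mean, SD, target difference or power. Its sample size (94 per group, 112 after attrition, Section 2.7) is for falls and does not bear on this point. All SPPB inputs below are assumptions.

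**Step 1: what an informative baseline gives.** With baseline-to-final correlation rho, ANCOVA multiplies the residual variance of the final score by 1 − rho².

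- rho = 0.3: 1 − 0.09 = 0.91
- rho = 0.5: 1 − 0.25 = 0.75
- rho = 0.7: 1 − 0.49 = 0.51

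**Step 2: what a constant baseline gives.** If every baseline equals the same value c, the covariate drops out of the model and the factor is 1. Change is the final score minus c, so its between-group difference and standard error are those of the final score. Both analyses reduce to an unadjusted comparison of final scores.

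**Step 3: between the extremes.** A simulation used 90 per arm (112 × 0.8 = 89.6) and 3000 runs per setting. It assumed SD 2.5, a true difference of 1 point and rho 0.6. Scores were rounded and limited to 0–12. For a partial floor, the patients with the poorest underlying mobility were set to zero and the rest scored above it.

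| Share of baselines at zero | Power, final score only | Power, change | Power, ANCOVA |
|---|---|---|---|
| 0% (informative) | 0.75 | 0.83 | 0.91 |
| 80% | 0.76 | 0.84 | 0.83 |
| 95% | 0.76 | 0.78 | 0.78 |
| 100% | 0.75 | 0.75 | 0.75 |

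The simulation error near 0.75 is about √(0.75 × 0.25 / 3000) = 0.008. The type I error was 0.047 to 0.054 in every setting and for every analysis. The floor therefore costs precision and does not bias the group comparison. The partial-floor rows are favourable to the plan, because they assume that scores above zero still rank patients by the mobility that predicts the final score.

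**Step 4: the sections on timing, side by side.**

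- Section 2.4 enrols a patient only once eligibility is met, but places every baseline measurement before surgery.
- Section 2.2.1 needs a postoperative weight-bearing status. Section 2.2.2 says that most, not all, patients with these procedures are allowed full weight bearing, so the planned procedure does not settle the criterion in advance.
- Section 2.4 lists the type of surgical repair among the baseline items. That is certain only after the operation.
- Section 2.2.2 does not say when the one-metre walking exclusion is judged.
- Section 2.8 assigns envelopes in order of recruitment without placing this before or after surgery.

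These statements do not all fit a wholly preoperative baseline.

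**The case against.** The strongest reply is that the floor is inferred. No section gives a baseline SPPB distribution. If the walking exclusion is applied before surgery, everyone enrolled can walk more than a metre with help, and some scores may exceed zero. The repair-type item also suggests that the sentence on preoperative timing may be loose drafting. The first part stands: the floor is a strong inference from the tasks and the injury, but not a stated fact. Loose drafting would not remove the problem, because this is the only timing given and staff would follow it. Nor is it a detail left to an analysis plan, since the article states the choice.

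A reader might infer that the SPPB analyses are empty. The documents do not support that. Randomisation keeps the comparison of final scores valid, and part of the precision gain survives if some scores are above the floor.

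A reader might also infer that patients are randomised before eligibility is known, which would lead to post-randomisation exclusions and a breach of intention to treat. The text does not fix that sequence. Section 2.4 requires eligibility to be met and the surgeon's clearance to be obtained, eligibility is checked from medical records, and the flow chart is not available here. What stands is only the need to reconcile the sections.

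It is also fair to say that the SPPB is secondary, that the change-from-baseline sentence does not name it, and that a test soon after arthroplasty may itself score low. The factors in Step 1 are therefore an upper range for what moving the test could recover.

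**Conclusion.** The point holds as a should-fix for a secondary outcome. As written, the only mobility baseline is preoperative and probably at or near the minimum. Adjusting for it would then add little or nothing to a comparison of final scores, and SPPB change would be hard to interpret.

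The precision forgone cannot be fixed from the protocol. Relative to a baseline with correlation 0.3, 0.5 or 0.7, it is a 9%, 25% or 49% reduction in residual variance (1 minus 0.91, 0.75 and 0.51), and less if an early postoperative test correlates more weakly. In the illustrative simulation, ANCOVA power falls from 0.91 to 0.78 with 95% of baselines at zero and to 0.75 with all at zero.

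The conclusion rests on the inference that patients with an unrepaired fracture largely cannot perform these tasks. It does not extend to the primary outcome: the falls model adjusts for baseline fall rates and does not use the SPPB. Nor does it extend to history items, which can properly be collected before surgery.

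**What to change.** In Section 2.4, take the baseline SPPB after surgery and before discharge, so before the home programme starts, and before allocation is revealed. That last condition matters because physiotherapists score the test and will know the group (Section 2.9). In Section 2.10, name this score as the ANCOVA covariate for the SPPB. Keep prior falls, pre-fracture function and demographics preoperative.

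Reconcile Sections 2.2.1, 2.2.2, 2.4 and 2.8 so that the order of eligibility, baseline and envelope opening is explicit and eligibility is confirmed before randomisation. When the walking criterion is to be judged is for the investigators to state.

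The cost is mainly protocol wording: the same staff give the same test somewhat later, during the same hospital stay. The downside is that the baseline then reflects the early postoperative state and may itself be low, so the gain is not guaranteed. The change is best made before recruitment, because a postoperative baseline that was not taken cannot be recovered.
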